#### Power calculation

We estimate that a sample of 162 patients will allow us to detect a mean difference of 1.476 in their empowerment in healthcare (corresponding to an effect size of 0.6) between our two groups. Assuming a standard deviation of 2.46 and an ICC (intraclass correlation coefficient) of 0.02, such a sample would give us a statistical power of 88% to detect the proposed mean difference at a significance level of 5% (Table 4). To account for an attrition and missing data rate of 10%, we have set a target of 180 patients. A previous study conducted by our research team yielded an ICC of 0.02 in a similar setting when measuring the frequency with which clinicians prescribed antibiotics after training in SDM [64]. We estimate that this convenient sample of 162 patients post intervention will allow us to detect a mean difference of 2.6% (SD = 4.8, Cohen’s D = 0.55) in decisional comfort (Decisional Conflict Scale) considering an ICC of 0.02 at a significance level of 0.05 and with a power of 80%.

**Table 4 Tab4:** Effect of study length on the power of the study

Scenario	Estimated power	Threshold of statistical significance	HCEQ Standard Deviation	Minimum detectable difference (Cohen’s effect size of 0.6)	Intra-cluster correlation	Adjusted standard deviation	Number of clusters (clinics)	Totalsample size	Study length (months)	Mean number of patients per clinic
1	0.519	0,05	2.46	1.476	0,02	2.65	6	54	1	9
2	0.76	0,05	2.46	1.476	0,02	2.85	6	108	2	18
3	0.88	0,05	2.46	1.476	0,02	2.98	6	162	3	27
4	0.92	0,05	2.46	1.476	0,02	3.21	6	216	4	36
5	0.948	0,05	2.46	1.476	0,02	3.37	6	270	5	45
6	0.963	0,05	2.46	1.476	0,02	3.53	6	324	6	54

Despite a relatively small number of clusters (six clinics to be randomized), we are confident that practice variation will be low enough to allow similar groups at baseline. Indeed, a recent systematic literature review reports rather uniform and low adoption of shared decision-making in the general practices in Canada, with two studies reporting OPTION scores of 24 ± 8 on a scale of 0–100 for one study (*n* = 152) and 19 ± 7 (*n* = 41) for the other.

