#### Data analysis

We will evaluate response rates as the number of clinics recruited divided by the number invited and the number of clinicians who agree to participate in the study divided by the number invited. We will also calculate patient recruitment rates as the number of patients recruited per attending physician per day. Audio-recordings of consultations will be collected by the research team at the end of each day and transcribed verbatim. Two trained research assistants will analyze the transcripts independently using the OPTION-5 scale [50–52] to quantify patient/caregiver involvement in the decision-making process during consultations.

We will perform descriptive statistical analyses of all the outcomes and measures. To compare the two study arms on primary and secondary outcomes, we will use hierarchical models to take into account the clustering effects of clinics and clinicians, intervention version, and repeated measures (for outcomes measured three times or more). For clinician-based outcomes, the analysis will take into account the decision considered, clinical site, sociodemographic characteristics of clinicians, and rural/urban localization of the clinic. For patient-based outcomes, the analyses will take into account clinical site, sociodemographic characteristics and dementia severity of patients, and rural/urban localization of the clinic. We will analyze all data following intention-to-treat principles. Quantitative data will be analyzed using the SAS statistical package (version 9.4).

To verify intervention fidelity, we will perform a concurrent analysis of the implementation processes (patient involvement in decision-making).

For each variable analyzed, according to the type of variable (continuous or categorical), the goodness of fit and the assumptions of each model will be assessed. We will analyze all data following intention-to-treat principles. Additionally, if the number of missing data is relatively low, then, in addition to analyzing the data by excluding missing observations, we will also perform a multiple imputation procedure on the full model and verify that results were not affected by missing information.

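### Agreement between complete-case analysis and multiple imputation cannot verify that outcomes missing at home follow-up left the results unaffected

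*Protocol article*

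**What the plan says.** The Phase 2 Data analysis section names two analyses and the conclusion to draw from them. One is the analysis without incomplete records: "in addition to analyzing the data by excluding missing observations". The other is multiple imputation: "we will also perform a multiple imputation procedure on the full model and verify that results were not affected by missing information". The second is run only "if the number of missing data is relatively low", and no threshold is given.

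The section does not define the full model or list the imputation variables. For patient outcomes it says that "the analyses will take into account clinical site, sociodemographic characteristics and dementia severity of patients, and rural/urban localization of the clinic". The baseline value of the outcome is not in that list. Repeated-measures modelling is reserved for outcomes taken at three or more times, and Table 3 lists the HCEQ twice, at t0 and t2.

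The Power calculation section sets the expected loss: "To account for an attrition and missing data rate of 10%, we have set a target of 180 patients".

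**The concern.** The text fixes an inference, not only a method: if the two analyses agree, missing data are held not to have mattered. Both analyses rest on the same kind of assumption, that missing outcomes resemble observed ones given the variables used. Comparing them cannot test that assumption.

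The outcomes exposed are those collected at the home visit after the consultation: HCEQ, QoL-AD, caregiver burden and decisional regret. In people with dementia, loss related to decline is plausible. Table 3 lists the patient's own HCEQ at follow-up only for able patients, so a patient who becomes unable in between could lose that measurement for a reason related to its value. A biased arm difference could then be published with a statement that missing data had been checked and did not matter.

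**Working it through.** **Inputs from the Power calculation section:** 180 recruited, 162 analysed, 6 clinics, 27 analysed per clinic, SD 2.46, ICC 0.02, target difference 1.476, 10% missing. **Assumed here:** three clinics per arm (90 recruited and 81 observed per arm), two-sided 5% test, normal outcome, 20 imputations, and the dropout mechanisms below.

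**1. The plan's own figures.** Design effect = 1 + (27 − 1) × 0.02 = 1.52. Adjusted SD = 2.46 × √1.52 = 3.03 (Table 4 prints 2.98). SE of the difference = 3.03 × √(2/81) = 0.477. Power = Φ(1.476/0.477 − 1.96) = 87.2%, or 88.3% with 2.98, against the stated 88%. Recruitment target: 162/0.9 = 180. The figures reproduce.

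**2. Why imputing from the analysis model returns the same estimate.** Let b be the complete-case estimate, with observed rows Xo and missing rows Xm. Imputed outcomes are Xm b* + e*, where b* is drawn around b and e* around zero. Refitting to the completed data gives (X′X)⁻¹(Xo′Xo b + Xm′Xm b* + Xm′e*). Its expectation is (X′X)⁻¹(Xo′Xo + Xm′Xm) b = b. The reason for dropout does not enter.

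**3. Size of the noise.** With 9 of 90 missing per arm, the completed arm mean differs from the observed one by 0.1 × 2.46 × √(1/81 + 1/9) = 0.086 (SD, one imputation). Over 20 imputations and two arms: 0.086/√20 × √2 = 0.027. Half the SE in step 1 is 0.238, nearly nine times this. With a covariate correlated 0.3 with the outcome, the noise is 0.027 × √(1 − 0.09) = 0.026, which matches the first simulation below.

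**4. Worst case for one arm, in closed form.** Losing exactly the lowest 10% of a normal distribution raises the arm mean by 2.46 × 0.1755/0.9 = 0.48 points. Adjusting for that covariate leaves about 0.48 × (1 − 0.09) = 0.44. If both arms lost their lowest 10%, both means would rise by 0.48 and the difference would not move.

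**5. First simulation** (1,500 trials per scenario, 10% missing per arm, random in control). Bias was 0.00 with random dropout in both arms, 0.302 with moderate dependence on the unseen outcome in the experimental arm, and 0.426 to 0.431 when the lowest 10% were lost. Complete-case and imputed biases matched to within 0.001. The SD of their difference was about 0.026 in every scenario, harmless or not.

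**6. Second simulation** (600 trials per scenario, no true effect, 180 patients; dropout log-odds slope 1.5 per SD of its driver; baseline correlation 0.5). Dropout is control/experimental. Agreement means estimates within 0.5 SE.

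| Dropout and driver | Complete-case bias | Imputed bias | Agreement |
|---|---|---|---|
| 10%/10%, unseen outcome, one arm | 0.232 | 0.233 | 100% |
| 5%/15%, unseen outcome, one arm | 0.328 | 0.327 | 100% |
| 5%/15%, same, baseline in neither model | 0.407 | 0.407 | 100% |
| 10%/10%, unseen outcome, opposite directions | 0.450 | 0.452 | 100% |
| 20%/40%, covariate in both models (harmless) | 0.006 | 0.003 | 100% |
| 20%/40%, unseen outcome, one arm | 0.791 | 0.787 | 100% |
| 5%/15%, auxiliary variable in the imputation model only | 0.213 | 0.001 | 27% |
| 5%/15%, baseline in the imputation model only | 0.211 | 0.002 | 44.5% |
| 5%/15%, unseen outcome, baseline in the imputation model only | 0.428 | 0.326 | 90% |

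In the first six rows both models use the same covariates, and agreement is complete whether the bias is near zero or large. In the next two, imputation has the variable that drives dropout and the comparison usually reveals the bias. In the last, it has a useful auxiliary variable, yet dropout still depends on the unseen outcome: the analyses agree in 90% of trials with a bias of 0.33 left in.

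**7. Relative size at 10% missing overall.** One arm only: 0.232/1.476 = 16% to 0.431/1.476 = 29%. Opposite directions: 0.452/1.476 = 31%.

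**The case against.** The strongest objection is that full model is undefined. It may mean refitting the adjusted analysis to data imputed with richer information. The baseline HCEQ, QoL-AD and burden scores are collected, and nothing excludes them from imputation. This stands: a reader might infer that the plan prescribes imputation from the analysis model alone, and the text does not establish that. Step 6 shows that auxiliary variables can make the comparison informative.

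Second, a reader might infer that the check passes almost always. The text speaks of missing observations generally. Where covariates are missing, imputation recovers patients whose outcomes were observed, and the two estimates can differ. The simulations had no missing covariates, and the plan states no pass criterion; 0.5 SE is a choice made here.

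Third, a reader might infer that every primary result is exposed. Table 3 also labels the Decisional Conflict Scale a patient primary outcome, and it is completed right after the consultation, so follow-up dropout does not reach it.

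Fourth, the sizes rest on dropout that depends on the unseen outcome and differs by arm. Nothing in the document shows that this will happen. The 20%/40% rows exceed the planned 10%, and the check might not be run at that level.

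Finally, imputation variables and missing-not-at-random analyses are usually left to the analysis plan, so their absence is no error in itself. What remains is the conclusion that the protocol does state. No comparison of two missing-at-random analyses supports it, with or without auxiliary variables.

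**Conclusion.** The stated inference does not follow. For outcomes missing at home follow-up, agreement between the two analyses cannot verify that results were unaffected, because both assume missingness at random. If missing follow-up outcomes are imputed only from the analysis covariates, agreement is built in and says nothing about dropout. That condition is the natural reading, but the text does not confirm it.

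As an illustration at 10% missing, with dropout that depends on the unseen HCEQ value in one arm only, both analyses carry a bias of about 0.23 to 0.43 points, 16% to 29% of the target difference. Opposite patterns in the two arms give about 0.45 (31%); similar patterns largely cancel. These are not forecasts. The logical point does not depend on them, and the planned main analysis is not invalidated. What needs correcting is the robustness claim.

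**What to change.** Revise the missing-data sentence in the Phase 2 Data analysis section in three ways.

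- **(a) Imputation model.** State that it includes arm and clinic and variables already collected but not listed for the analysis model: t0 HCEQ, QoL-AD and caregiver burden; t1 Decisional Conflict Scale and CollaboRATE; and the caregiver's own reports.
- **(b) Sensitivity analysis.** Add a delta-adjusted imputation by arm, which shifts imputed follow-up values over a range that the trial team prespecifies, and report the delta at which the conclusion changes.
- **(c) Wording.** Replace the promise to verify that missing information had no effect with a statement that robustness is claimed only to the extent that (a) and (b) show it.

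The cost is a paragraph of text and some extra SAS programming. No new data or patients are needed. The article says Phase 2 data were still being collected, so on that account the wording could be fixed before analysis. The downside is that the robustness statement may turn out less favourable.

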## Discussion

By designing tools that help healthcare professionals empower seniors to make clinical decisions on issues that affect their own health, this initiative supports seniors’ wellbeing and independence, the latter being one of the four principles of healthy aging [65]. The training program will provide clinicians, patients living with dementia, and their caregivers access to best available evidence on health options, so that together they can decide on next steps. In their role as partners in decision-making, seniors and their caregivers will experience more decisional comfort and have higher levels of perceived healthcare empowerment, while allowing identification of their priorities. Ultimately, this training program will ensure that patients and caregivers make informed decisions that reflect their care goals and values.

The self-learning format ensures accessibility in all regions with online access, even the most remote. The scientific information will be made available broadly to all stakeholders: physicians and residents; nurses and other health or social services professionals; patients and their caregivers. This continuity of information among the various stakeholders will ensure better coordination of care and services between the parties, resulting in better monitoring of care and support of seniors with cognitive impairment. We expect that these tools will become an essential reference for the training of health professionals across the province of Quebec and for patients with cognitive impairment and their caregivers.

Ultimately, this project will meet the training needs of clinicians who care for seniors with cognitive impairment in Quebec. Indeed, our partners and users associated with continuing professional development (CPD) have committed to implement, disseminate and build on project deliverables. Specifically, the CPD sector of the Office of Education and Continuing Professional Development of the Faculty of Medicine at Laval University will offer our e-learning training program to health professionals of every primary care organization in Quebec. We will also draw on our excellent relations and involvement in the network of the 12 teaching family medicine units of the (RUIS-Laval) and in the frontline research Network, Réseau-1 to raise awareness of the tools to users. The revenues generated through the credits for CPD course will allow to sustain the training program, notably to update the DBs and expand the program to offer DBs on additional topics.

Patient recruitment is critical in this project. Our experience in recruiting clinicians in primary care settings ensures that we will complete this important step. The delayed intervention allows that all recruited clinicians are exposed to the training program, thus facilitating recruitment. In addition, seniors living with dementia are typically underdiagnosed in primary care. Consequently, we will collaborate with the Quebec Alzheimer Plan, an implementation initiative currently underway in the Province [66], which aims to improve the identification of patients living with dementia in primary care settings. This partnership will allow targeting clinicians already trained in the identification of seniors living with dementia and a more rapid identification of key stakeholders to help with recruitment.

### Strengths and limitations

Our study of a user-centered approach will mainly rely on qualitative evaluations, which will provide rich findings to draw some first conclusions on how the approach influences the vulnerable patients’ and their caregivers’ experiences of the DBs. The quantitative results will allow preliminary conclusions on the extent to which the approaches improve implementation, due to a limited sample size that could prevent statistical significance. This study is also limited because we chose to assign tools to patient/caregiver dyads randomly, to ensure an equal number of evaluation for each tool. Consequently, the tools that participants will get might not be those they would have preferred to answer their current questions, and so this deviates from daily practice.

The pragmatic clustered RCT is the best design to draw conclusions on the impact of a complex intervention on patient-important outcomes. However, due to its complex nature, several aspects of the intervention will be challenging to control. We cannot control if the clinicians will complete the distance training program and offer the DBs to their patients, but the user-centered development improves the odds that these tools will be adopted in practice. We do not either control if the participants will want to discuss the decisions covered in the studied DB during the consultations, but the fact that some of these decisions can be discussed by participants at any stage of the disease, and that they are typically rarely discussed (e.g. choosing a support option for the caregiver, preparing advance directives and a protection mandate), will encourage their use.

### Recruitment status

 Recruitement is completed. We are currently collecting data for Phase two (Fig. 4).

**Fig. 4 Fig4:**
[figure not shown]
Project timeline

## Abbreviations

BPSD: Behavioral and Psychological Symptoms of Dementia
C-DB: Clinician Decision Box
CPD: Continuing professional development
IAM: Information Assessment Method
ID: Identification
P-DB: Patient-Decision Box
RCT: Randomized controlled trial
SDM: Shared decision-making
TAM: Technology Acceptance Model
TPB: Theory of Planned Behavior
